### Patient follow-up

Prospective collection of the follow-up data will be carried out postoperatively via three bimonthly telephone interviews over the initial 6 months. Three surgical residents will perform the acquisition of the follow-up data. The telephone interview will be based upon a customized questionnaire, which incorporates information critical to the present study. Follow-up data will then be stored in a central database. Patients in whom the interview revealed equivocal information pertinent to the study will be asked to consign their medical records for further review by a cardiac surgeon and a cardiologist blinded to the study protocol. In the case that the opinions of the two reviewers differ, a third reviewer will offer an opinion, which will then be considered definitive and will be stored in the central database.

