### Randomization of patients and interventional strategy

All post-CABG patients in whom none of the postoperative exclusion criteria have occurred will undergo MEA analysis on postoperative day 4. Patients found to have evidence of ASA low-responsiveness, as defined by an ASPI test ≥ 30 AUC, will undergo randomization into either the control group or the dual antiplatelet therapy (dAPT) group. Assignment to either group will be performed by random allocation using randomization software [15]. Patients in the control group will continue to receive 300 mg of ASA in accordance to our hospital’s standard post-CABG antiplatelet management strategy. Patients in the dAPT group will, conversely, be subjected to augmentation of their antiplatelet regime by receiving 75 mg of clopidogrel in addition to the 300 mg of ASA. A flowchart depicting the screening and randomization protocols is shown in Figure 1.

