### Outcome definitions

The primary clinical endpoint of the study will be the incidence of major adverse cardiac and cerebrovascular events (MACCE) in relation to two distinct antiplatelet strategies (ASA monotherapy or dual antiplatelet therapy) in patients found to be ASA-resistant. MACCE will be defined as a composite endpoint consisting of all-cause mortality, non-fatal myocardial infarction, cerebrovascular accident and cardiovascular rehospitalization. The definition of perioperative and postoperative myocardial infarction will be based upon published recommendations of the Joint European Society of Cardiology/American College of Cardiology Foundation/American Heart Association/World Heart Federation Task Force for the Redefinition of Myocardial Infarction [20]. The definition of stroke will be based upon a new onset focal neurological deficit lasting > 24 hours or an imaging study suggestive of an acute clinically relevant cerebral lesion in patients with rapid recovery [21].

Bleeding events will constitute the secondary clinical endpoint. They will be stratified in accordance to the consensus report from the Bleeding Academic Research Consortium (BARC). In brief, the hemorrhagic complications according to the BARC scale range from type 1, which denotes bleeding that is not actionable, to type 5 which is defined as a bleeding-related fatal event [22]. Type 0 denotes the absence of bleeding [22].

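### The reviewers of equivocal events are blinded to the study protocol, but nowhere to treatment allocation, so the stated masking does not ensure that the arm is concealed

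*Protocol article*

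**What the plan says.** Outcomes are collected by telephone every two months for six months: "Three surgical residents will perform the acquisition of the follow-up data" (protocol article, Patient follow-up). The same section adds a second step for unclear cases: "Patients in whom the interview revealed equivocal information pertinent to the study will be asked to consign their medical records". The masking rule for that step is worded as "further review by a cardiac surgeon and a cardiologist blinded to the study protocol". If the two disagree, "a third reviewer will offer an opinion, which will then be considered definitive". No masking of any kind is attached to that third opinion.

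The treatments are set out under Randomization of patients and interventional strategy. "Patients in the control group will continue to receive 300 mg of ASA", while the other arm has its regimen augmented by "receiving 75 mg of clopidogrel in addition to the 300 mg of ASA". No placebo is mentioned.

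The primary endpoint, under Outcome definitions, is a "composite endpoint consisting of all-cause mortality, non-fatal myocardial infarction, cerebrovascular accident and cardiovascular rehospitalization". Criteria are fixed there as well: "The definition of perioperative and postoperative myocardial infarction will be based upon published recommendations", stroke has a stated definition with a cited source, and bleeding is graded on the BARC scale.

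**The concern.** Event review protects a trial when the person judging the event does not know which treatment the patient received. Not knowing the protocol is a different matter: a reviewer can be unaware of the protocol and still read the drug list. The article did choose to state a masking rule for its reviewers, so this is a matter of what the rule says and not only of silence.

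Equivocal cases are the ones in which judgement decides whether an event counts. All components of the primary endpoint other than death need some judgement, and so does the grade of a bleed. A reviewer who sees clopidogrel may be slower to confirm an ischaemic event and quicker to confirm or upgrade a bleed. That would favour dual therapy on the primary endpoint and count against it on the secondary one.

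A separate and lesser issue is that reviewers who have not been given the trial's definitions may use their own. If they do not know the arm, this mainly adds noise to both arms and creates no directional difference.

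**Working it through.** No figure in the plan depends on this point, so there is none to reproduce, and the fix changes neither the sample size, the power nor the significance level. The check sets the statements side by side.

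1. **Object of masking.** Patient follow-up names the study protocol. No section states blinding to allocation for the two reviewers, the third reviewer or the interviewing residents. The Blood sampling section does state that the person running the aggregometry has no part in care or follow-up, so the article describes such safeguards in places.

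2. **Could the arm show?** The reviewers' source is the patient's own records. The planned difference between the arms is clopidogrel, with no placebo described and no masking of records stated. That the records list clopidogrel is an inference, though a likely one. Under Preoperative antiplatelet therapy management, some patients take clopidogrel before surgery, so an old entry does not identify the arm. A current postoperative entry is more telling, because Study population excludes patients with a medical condition for which dual therapy is indicated.

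3. **Masking against task.** The reviewers must decide whether a case meets the definitions under Outcome definitions. Those definitions are part of the protocol, and Patient follow-up does not say that they are supplied separately. Read literally, the two sections pull against each other. They are compatible if the definitions are handed over on their own.

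4. **Who is affected.** Only cases with an unclear interview reach these reviewers. All others rest on the residents' interviews.

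5. **Size.** If m equivocal ischaemic cases per arm are reviewed, and the proportions confirmed are c(control) and c(dual), then with equal true rates the spurious gap is m × (c(control) − c(dual)). The document gives none of these inputs. Purely as an illustration, assume 0.60 and 0.40, a difference of 0.20:
   - m = 3: 3 × 0.20 = 0.6 events
   - m = 10: 10 × 0.20 = 2 events
   - m = 20: 20 × 0.20 = 4 events

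   The answer runs from negligible to noticeable, depending wholly on assumed inputs.

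**The case against.** The strongest reply is that the phrase is loose wording for blinding to study assignment, and that a condensed article need not describe how records are prepared or how a third reviewer is masked. Both may be true. The silence about the third reviewer would not be a finding alone. What stands is that a rule is stated and its object is not allocation. If allocation was meant, the correction is a few words.

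A second reply is that a reviewer truly ignorant of the protocol would not know the arms or the hypothesis, so seeing clopidogrel would carry less expectation. This weakens the mechanism but does not remove it, since a cardiologist or surgeon brings general expectations about what the drug does to clotting and bleeding.

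A reader might go further and infer that the reviewers do see who received clopidogrel, or that the definitions are withheld from them. The document supports neither. It does not say that allocation is disclosed or that records are left unredacted. The infarction and bleeding criteria, and the source cited for stroke, are published and could be supplied without the protocol.

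**Conclusion.** The point holds in limited form. The stated masking does not ensure that treatment allocation is concealed from those who decide equivocal events, and its literal wording fits poorly with the definitions they must apply. This rests on two readings: that no placebo is used, since none is described, and that medical records would ordinarily list clopidogrel.

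The effect is confined to equivocal cases, and its size cannot be derived from the document. A reader might divide 2 to 4 spurious events by about 10 (219 × 0.9 = 197.1, so about 99 per arm if allocation is equal, and 10 points of that) and conclude that review bias could supply 20 to 40% of the target effect. That is not supported. The case numbers and confirmation rates have no source, and smaller numbers give far less. The cases sent for review may include bleeding, which is a separate endpoint. The Sample size section also does not say that its 10% means percentage points.

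The correction should be made because it is cheap and bears on both endpoints, not because a large bias has been shown.

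**What to change.** In Patient follow-up, replace the masking phrase so that the reviewers are *blinded to treatment allocation and supplied with the endpoint definitions given under Outcome definitions*. State that the same applies to the third, deciding reviewer. Add that the study office masks antiplatelet drug names and any arm label in the records before review. Masking should be done identically in both arms, with a neutral placeholder, so that the redaction does not itself reveal the arm.

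The cost is a sentence or two of text and clerical time for each reviewed case. No extra reviewers are needed. Masking may be imperfect, because free text in records supplied by patients can still reveal treatment. Recruitment is described as ongoing, so the change can apply to reviews still to come. It does not alter how clear cases are classified from the residents' interviews.

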### Outcome definitions

The primary clinical endpoint of the study will be the incidence of major adverse cardiac and cerebrovascular events (MACCE) in relation to two distinct antiplatelet strategies (ASA monotherapy or dual antiplatelet therapy) in patients found to be ASA-resistant. MACCE will be defined as a composite endpoint consisting of all-cause mortality, non-fatal myocardial infarction, cerebrovascular accident and cardiovascular rehospitalization. The definition of perioperative and postoperative myocardial infarction will be based upon published recommendations of the Joint European Society of Cardiology/American College of Cardiology Foundation/American Heart Association/World Heart Federation Task Force for the Redefinition of Myocardial Infarction [20]. The definition of stroke will be based upon a new onset focal neurological deficit lasting > 24 hours or an imaging study suggestive of an acute clinically relevant cerebral lesion in patients with rapid recovery [21].

Bleeding events will constitute the secondary clinical endpoint. They will be stratified in accordance to the consensus report from the Bleeding Academic Research Consortium (BARC). In brief, the hemorrhagic complications according to the BARC scale range from type 1, which denotes bleeding that is not actionable, to type 5 which is defined as a bleeding-related fatal event [22]. Type 0 denotes the absence of bleeding [22].

### Statistical analysis

The continuous data will be presented as mean values ± standard deviation (SD) or medians with their respective interquartile range. Categorical variables will be presented as absolute numbers with percentages. Analyses of continuous data between different groups of patients will be performed using the Mann-Whitney *U*-test. Differences between categorical variables will be evaluated with Fisher’s exact test. A two-tailed *P*-value will be used amd *P* < 0.05 will be considered significant for all deployed statistical calculations. The data will be processed using the Statistica 9 software package (StatSoft Inc., Tulsa, USA).

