### Individual variability to antiplatelet agents

The incidence of interpatient variability to antiplatelet drugs depends upon the laboratory evaluation used to diagnose it [7]. Novel tools for quantifying drug induced platelet inhibition have brought into focus the individual variations in antiplatelet responses. This underscores the importance of identifying the optimal antiplatelet drug protocol in order to achieve the targeted level of anti-aggregation. Multiple electrode aggregometry (MEA) has been shown to be a useful instrument in the quantification of platelet inhibition by ASA [6]. Its mechanism of assessing platelet inhibition is based on changes in impedance on its sensor wires secondary to platelet adherence. Aspirin resistance has been suggested to range anywhere from 1 to 45% [7]. The efficacy of ASA absorption, TXA2 independent platelet activation pathways, COX-1 gene mutations, as well as ASA interactions with other medications have all been postulated to play a role in inducing aspirin resistance [9]. The response to ASA should best be viewed as a continuous variable. Dichotomizing patients into responders or non-responders is, however, suitable for scientific research and is commonly employed for this purpose [7]. The presence of ASA low-responsiveness has been linked to an increase in cardiovascular morbidity [9]. The clinical correlation of individual patient refractoriness to ASA with an increased incidence of cardiovascular complications is fundamental to the present study. This will be, to the best of our knowledge, the first prospective randomized study that will aim to evaluate whether the combination of ASA and clopidogrel in ASA-resistant CABG patients offers a clinical benefit. Our hypothesis that a dual antiplatelet regime will improve patient outcomes in this setting stems from the convergence of the clinical impact of ASA resistance and the benefit gained from adding clopidogrel to ASA in certain clinical scenarios.

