### Sample size

An exact binomial test power analysis was performed in order to estimate the approximate sample size required to test the null hypothesis. The minimum effect size was 10%. Accounting for a maximum estimated 10% loss to follow-up, a total of 219 patients will be required to test the null hypothesis with an α value of 0.05 and a power of 0.8.

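### The implied Fisher's exact test for MACCE is valid but conservative; a log-rank test, or Boschloo's test if the comparison stays binary, would gain a few points of power at almost no cost

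*Protocol article*

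**What the plan says.** The Outcome definitions section makes the incidence of MACCE the primary clinical endpoint. Patient follow-up schedules three telephone interviews, two months apart, over 6 months.

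Statistical analysis names two tests: Mann-Whitney for continuous data and Fisher's exact test for categorical data ("Differences between categorical variables will be evaluated with" that test). It adds "A two-tailed *P*-value will be used", with significance at P < 0.05 for every calculation. MACCE is not given its own test, but no other named method fits it.

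The Sample size section states "An exact binomial test power analysis was performed", "The minimum effect size was 10" per cent, and "a total of 219 patients will be required to test the null hypothesis" "with an α value of 0.05 and a power of 0.8". Loss is anticipated: "Accounting for a maximum estimated 10% loss to follow-up".

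On the platelet assay, the Background says "The response to ASA should best be viewed as a continuous variable". The next sentence accepts splitting patients into responders and non-responders for research. The ASPI value is measured on postoperative day 4, before randomisation, and entry requires at least 30 AUC.

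**The concern.** The plan commits to a specific test, so this is a choice that can be judged, not a detail left to another document. Two properties of that choice matter.

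- Fisher's test conditions on the total number of events. With a few dozen events the attainable P-values are coarse, so the test rejects less often than 5% under the null and loses power.
- A 2×2 table needs a yes or no for every patient. A patient last reached at month 2 or 4 without an event has known event-free time that the table cannot hold.

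Under most plausible event rates 219 patients give low power for a 10-point difference, so a few points available from the wording of the analysis are worth having.

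**Working it through.** **Inputs from the protocol:** total 219, up to 10% loss, two-sided alpha 0.05, power 0.80, effect 10%, 6 months, three contacts.

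**Assumptions, because the protocol gives no figure:** 1:1 allocation, the MACCE rates shown below, the effect read as 10 percentage points, and the timing of events and losses.

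**1. The plan's own figure.** A one-sample exact binomial test of 0.50 against 0.60 (both values assumed), two-sided 0.05, first reaches 80% power at n = 199 (power 0.804). Then 199 × 1.10 = 218.9, or 219. Dividing instead gives 199 / 0.90 = 221.1, or 222. The 219 is therefore reproducible, but as a one-sample calculation.

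For two arms at 20% vs 10%, n per arm = [1.96·√(2·0.15·0.85) + 0.842·√(0.20·0.80 + 0.10·0.90)]² / 0.10² = (0.990 + 0.421)² / 0.01 ≈ 199. That is 398 evaluable in total, and 398 / 0.90 = 442.2, or 443 randomised.

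**2. True size of Fisher's test.** Evaluable patients: 219 × 0.90 = 197.1, so 99 + 98. For a common event rate p, size = Σ Bin(x₁; 99, p)·Bin(x₂; 98, p) over all tables with Fisher P ≤ 0.05.

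- 99 + 98: 0.030 at p = 5%, 0.037 at 10%, 0.041 at 15%, 0.040 at 20%, 0.042 at 30%.
- 98 + 98: 0.021 at 5%, 0.028 at 10%, 0.032 at 20%, 0.035 at 30%. Exactly equal arms make the test still more conservative.

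**3. Power, Fisher on completers against log-rank on all randomised.** Simulation with 109 per arm, 6 months, 10% exponential loss, 4,000 runs (Monte Carlo error about 0.8 points):

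| Assumed MACCE | Fisher | Log-rank | Gain (points) |
|---|---|---|---|
| 12% vs 2% | 0.81 | 0.85 | 4 |
| 15% vs 5% | 0.63 | 0.68 | 5 |
| 20% vs 10% | 0.48 | 0.53 | 5 |
| 25% vs 15% | 0.40 | 0.45 | 5 |
| 30% vs 20% | 0.34 | 0.38 | 4 |
| 40% vs 30% | 0.29 | 0.33 | 4 |

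A second simulation used 110 + 109 patients with losses at 0, 2 or 4 months. At 20% vs 10% it gave 0.46–0.47 for Fisher and 0.51–0.52 for log-rank; at 15% vs 5%, 0.61–0.63 and 0.68. The gain is 5 to 7 points. Log-rank type I error was 0.047–0.050.

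**4. Where the gain comes from.** In the first simulation an uncorrected chi-square test on the same completers gave 0.68 at 15% vs 5%, 0.53 at 20% vs 10% and 0.38 at 30% vs 20%. These match log-rank to two decimals, so partial follow-up added under 1 point and the rest is Fisher's conservatism. When losses are placed at the contacts and every lost patient is excluded, the share from partial follow-up is somewhat larger but still the smaller part.

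**5. Staying binary.** Boschloo's test orders tables by Fisher's P-value and takes the largest cut-off whose size stays at or below 0.05 for every common event rate. At 99 + 98 and 20% vs 10%, exact power is 0.473 against 0.448 for Fisher.

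**6. Adjusting for ASPI.** Cox model, 2,000 runs, hazard ratio per SD of ASPI assumed. At 20% vs 10%, power without and with adjustment was 0.521 and 0.522 (hazard ratio 1.3), 0.517 and 0.529 (1.6), 0.508 and 0.541 (2.0). Across the scenarios the gain was about 0 to 1, 1 to 3 and 3 to 5 points respectively.

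**The case against.** The best defence is that nothing here is an error. A 6-month incidence with the same planned follow-up for everyone is naturally binary, a binary test fits the binomial sample-size calculation, and Fisher's test protects the type I error. All of that stands, so the point is about a better choice, not an invalid one.

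Four stronger readings might be inferred, and the documents do not support them:

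- *That unused partial follow-up is the main loss.* It is the smaller part (step 4). The protocol also sets no rule for lost patients in the analysis. Counting them as event-free would widen the gap to 5 to 8 points, but that handling is nowhere planned.
- *That leaving ASPI out contradicts the Background.* The sentence after the one quoted accepts dichotomising for research. The stated link between aspirin refractoriness and complications does not establish a gradient among patients already selected at 30 AUC or more, and the Discussion calls them a homogeneous group. No prognostic strength is given, so the gain from adjustment is unknown.
- *That changing the test repairs the trial's power.* It does not. The larger weakness is the sample-size calculation, which is a separate matter.
- *That estimates and confidence intervals are excluded.* The section is silent on them, and an article commonly leaves such detail to the full plan.

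The replacement has costs of its own. Censoring at last contact assumes loss unrelated to risk, and event dates would come largely from two-monthly telephone calls.

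**Conclusion.** The point holds at modest size. The implied primary test runs at a true level of about 0.03 to 0.04 instead of 0.05. A log-rank analysis of all randomised patients gains about 4 to 7 points of power over Fisher on completers, and Boschloo's test about 2.5 points at 20% vs 10% (0.473 − 0.448 = 0.025). Log-rank power remains at about 0.68 for 15% vs 5% and 0.51–0.53 for 20% vs 10%, below the stated 0.80; only near 12% vs 2% is 0.80 reached, and there Fisher on completers already gives about 0.81.

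These figures rest on assumed event rates, 1:1 allocation and simple patterns of loss. The direction of the difference was the same in every scenario examined.

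**What to change.** Make the primary analysis time from randomisation to first MACCE, in all randomised patients as assigned, censored at last successful contact. Test with the log-rank test, and report a Cox hazard ratio with 95% CI and the 6-month Kaplan-Meier risk difference with 95% CI.

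If the binary comparison is kept, replace Fisher's test with Boschloo's exact unconditional test, which keeps the 5% guarantee and is never less powerful than Fisher.

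Adjusting the Cox model for continuous day-4 ASPI AUC is optional. If used, it should be prespecified and not justified by a promised gain in power.

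The cost is revised analysis wording, an event-date field in the existing questionnaire and slightly more analysis work. The time-to-event version also takes on the assumption of non-informative loss, which should be stated. Recruitment is described as ongoing, so the change should be fixed before any comparison by arm is seen.
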